### Safety and discontinuation of treatment

Toxicities are classified by type, grade, duration, onset and relationship to radiation treatment. Severe acute gastrointestinal toxicity (≥ grade 3) is the main dose limiting factor in patients receiving adjuvant three-dimensional conformal radiation therapy after surgery. The safety analysis was designed to demonstrate that the combination of neoadjuvant intensity-modulated radiation therapy with surgery and intraoperative radiation therapy will not result in an increased rate of severe acute gastrointestinal toxicity. The rate of patients who will suffer from acute severe gastrointestinal toxicity in a comparable patient population treated with standard procedures (surgery followed by adjuvant three-dimensional conformal radiotherapy) was estimated to be 20%.

A toxicity related discontinuation criteria was implemented such that after having recruited about one third of the total number of patients an increase by 20% of the onset of severe acute gastrointestinal toxicities (from 20% to 40%) should be detected with a power of 80% at a level of significance of α = 5% in one interim analysis. Therefore, an optimal two-stage design
[23] was calculated which suggested to do an interim analysis after n1 = 15 patients among a total of 43 and to stop for toxicity when more than r1 = 5 patients would show severe gastrointestinal toxicity. Since the calculated sample size was n = 37, these numbers were adjusted to n1 = 13 and r1 = 4. Therefore, the study should stop for toxicity after 13 patients if ≥ 5 patients would have developed a severe acute gastrointestinal toxicity.

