### Sample size estimation, confirmatory and descriptive analyses

The primary endpoint of the trial is the local control rate after five years (LC-5yR). The study is designed to demonstrate that the combination of neoadjuvant dose-escalated intensity-modulated radiation therapy with surgery and intraoperative radiation therapy can improve the local control rate after five years. Local control rate after five years in a comparable patient population treated with standard procedures (surgery followed by adjuvant three-dimensional conformal radiotherapy) was estimated to be 50% according to the literature. The sample size calculation was designed on the assumption to detect an improvement by 20% in this primary endpoint. For sample size calculation, the following hypotheses have been made:

p0 is the largest LC-5yR which, if true, implies that the efficacy of the study treatment is too low. In the present trial P0 has been taken as 50%

p1 is the lowest LC-5yR which, if true, implies that the efficacy of the treatment is adequate. In the present trial p1 has been taken as 70%

α is the acceptance probability of considering adequate efficacy of the treatment with a true LC-5yR equal or lower to p0 (false positive decision). In the present trial α has been taken as 5%

β is the acceptance probability of rejecting adequate efficacy of the study treatment with a true LC-5yR at least equal to p1 (false negative decision). In the present trial β has been taken as 20%.

Using the one-sided binomial test (“Exact Test”) with the given hypotheses, the study requires 37 patients to decide whether the LC-5yR is less or equal to 0.5 or greater or equal to 0.7. If the number of locally controlled patients is ≥24, the hypothesis that LC-5yR is ≤ 0.5 will be rejected with a target error rate of 0.05. Sample size calculation and confirmatory analysis are based on the per protocol population
[22].

Secondary endpoints are all of explorative nature and reported using descriptive analysis methods. Time to event data (progression free survival, overall survival) will be evaluated using the Kaplan-Meier-Method.

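### The safety analysis is said to demonstrate no increase in severe acute GI toxicity, but the only rule given is a stop-only look at 13 patients, and passing it cannot show that

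*Protocol article*

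**What the plan says.** All references are to the protocol article.

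- *Safety and discontinuation of treatment* sets the aim. The safety analysis is designed to demonstrate that the combination "will not result in an increased rate of severe acute gastrointestinal toxicity". The reference is a rate of 20%, estimated for surgery followed by adjuvant three-dimensional conformal radiotherapy. No margin for an acceptable excess is given.
- The same section describes the decision rule as detecting a rise from 20% to 40% "with a power of 80% at a level of significance of α = 5% in one interim analysis". It starts from a two-stage design with an "interim analysis after n1 = 15 patients among a total of 43 and to stop for toxicity when more than r1 = 5 patients", and continues: "Since the calculated sample size was n = 37, these numbers were adjusted to n1 = 13 and r1 = 4". The operative rule is that "the study should stop for toxicity after 13 patients if ≥ 5 patients would have developed a severe acute gastrointestinal toxicity".
- *Study objectives and endpoints* lists acute toxicity among the secondary objectives.
- *Sample size estimation, confirmatory and descriptive analyses* says: "Secondary endpoints are all of explorative nature and reported using descriptive analysis methods". The 37 patients are sized on local control alone.

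**The concern.** The stated aim and the stated rule point in opposite directions. The rule takes 20% or less as its null hypothesis and acts only when the data speak for an increase. A demonstration of no increase needs the reverse: an unacceptable rate as the null hypothesis, and data that exclude it. A trial that sees 4 or fewer events in 13 patients has failed to reject 20%, and nothing more.

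The article describes no other inference that could carry the claim, because the toxicity endpoint is otherwise descriptive. This matters because the Background and the abstract's Discussion make better local control without markedly increased toxicity the aim of the trial. As written, a passed look at 13 patients could be reported as demonstrated safety.

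**Working it through.** **Inputs** (*Safety and discontinuation of treatment*): reference rate 20%; rate to be detected 40%; stop if 5 or more of 13, so the look is passed with 4 or fewer. Total of 37 from the sample size section.

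**1. The plan's own figures.** The article attaches 80% power and a 5% level to the interim look. For the rule of 5 or more of 13:

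- P(stop | 20%) = 1 − P(X ≤ 4 | 13, 0.2) = 1 − 0.901 = 0.099
- P(stop | 40%) = 1 − P(X ≤ 4 | 13, 0.4) = 1 − 0.353 = 0.647

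The look therefore has about 10% and 65%, not 5% and 80%. That mismatch is a separate matter. The present point would stand even if the stated error rates were met.

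**2. Chance of passing when toxicity is raised.** P(X ≤ 4 | 13, p) = Σ C(13,k) pᵏ(1−p)¹³⁻ᵏ for k = 0 to 4. At p = 0.4 the terms are 0.0013 + 0.0113 + 0.0453 + 0.1107 + 0.1845 = 0.353.

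| True rate | P(pass) |
|---|---|
| 20% | 0.90 |
| 30% | 0.65 |
| 35% | 0.50 |
| 40% | 0.35 |

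**3. What a passing result can exclude.** The exact two-sided 95% interval for 4/13 runs from the 0.025 quantile of Beta(4, 10) = 0.091 to the 0.975 quantile of Beta(5, 9) = 0.614. The one-sided 95% upper bound for x events in n is the 0.95 quantile of Beta(x+1, n−x):

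| Events in 13 | Upper bound |
|---|---|
| 0 | 20.6% |
| 1 | 31.6% |
| 2 | 41.0% |
| 3 | 49.5% |
| 4 | 57.3% |

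No passing result excludes every rate above 20%. Only 0 or 1 event excludes 40%, and P(X ≤ 1 | 13, 0.2) is 0.23.

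**4. What the full sample could show.** Take 40% as the rate to be excluded; this is an assumption, since no margin is stated. With n = 37, the largest count whose one-sided 95% upper bound lies below 40% is 9 (bound 38.6%; for 10 events it is 41.5%). Ignoring the interim, P(X ≤ 9 | 37, p) is 0.809 at p = 0.2 and 0.035 at p = 0.4.

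The interim stays, so a trial must pass both. With 37 − 13 = 24 patients after the look:

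P(accept) = Σ P(X₁₃ = k) · P(X₂₄ ≤ 9 − k), for k = 0 to 4

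This gives 0.771 at 20% and 0.031 at 40%.

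**5. Sensitivity to the number treated.** Accrual runs until the per-protocol number is reached, so the number who receive at least one fraction may exceed 37. The same formula, with the cutoff recomputed for each n:

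| n | Cutoff | Power at 20%, interim kept | False acceptance at 40%, interim kept |
|---|---|---|---|
| 37 | 9 | 0.77 | 0.031 |
| 38 | 9 | 0.75 | 0.024 |
| 39 | 10 | 0.81 | 0.039 |
| 40 | 10 | 0.79 | 0.031 |
| 41 | 10 | 0.77 | 0.024 |
| 42 | 11 | 0.82 | 0.038 |
| 43 | 11 | 0.81 | 0.030 |

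**The case against.** The strongest reply is that this is a stopping rule in a section on discontinuation. Nowhere does the article say that 4 or fewer of 13 proves safety. Toxicity is collected in all patients until three months after surgery and will be reported, and a confidence interval is an ordinary part of a descriptive report. A final toxicity analysis may also stand in the full protocol or the SAP, which are not shown.

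Much of this is fair, and it limits the point in four ways.

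- A reader might infer that the second-stage toxicity boundary was dropped. The article does not say so. It gives adjusted first-stage numbers and is silent on the rest.
- A reader might infer that the error of accepting 40% toxicity is uncontrolled. It is not: the look stops 65% of trials at that rate, which is weak but not nothing.
- A reader might infer that the toxicity question cannot be answered at all. The rule alone cannot answer it, but the full-sample data bear on it.
- A reader might infer that a final test in 37 patients would deliver the stated 5% and 80%. With the interim kept, power is 0.77.

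What does not fall is the conflict between two stated sentences: a safety analysis designed to demonstrate, and secondary endpoints that are all explorative. This does not rest on silence, and a SAP that added a confirmatory toxicity test would itself depart from the second sentence. If the rule is only a safeguard, the first sentence claims too much.

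**Conclusion.** The point holds as a mismatch between claim and design. The look at 13 patients can stop a trial with excess toxicity, but passing it does not demonstrate absence of an increase. A true 40% rate passes about one time in three (0.35), and 4/13 is compatible with rates from 9% to 61%.

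These figures assume independent patients with a common event rate and rest on the rule exactly as stated. The final-analysis figures also assume a margin of 40%. That is the only excess rate the article names, and it appears there as a rate to be detected, not as a non-inferiority margin. Excluding it would support the claim that the rate is below 40%, not that it is not increased. Ignoring the interim, a cutoff of 9 in 37 would still be met with probability 0.55 at a true 25% and 0.29 at a true 30%.

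The primary endpoint is unaffected. What changes is what the trial may conclude about safety.

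**What to change.** Describe the interim look as a safeguard against excess toxicity and nothing more. Then do one of the following:

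1. Withdraw the statement that the safety analysis is designed to demonstrate no increase, and report severe acute GI toxicity descriptively with an exact confidence interval.
2. State and justify a margin, and add one final analysis of severe acute GI toxicity in all patients who received at least one fraction. Compare the exact one-sided 95% upper bound with the margin. Exempt this analysis explicitly from the sentence that makes all secondary endpoints explorative.

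Under the second option, fix the method rather than a count, so that the cutoff follows the number actually treated. With a 40% margin it is 9 events at n = 37 and 11 at n = 43. Quote the operating characteristics with the interim included: power at a true 20% is about 0.75 to 0.82 for n from 37 to 43. Word the conclusion as a rate below the margin.

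The cost is a changed sentence or one added analysis of data already being collected, and a more modest safety claim. No new patients are needed and the stopping rule is left as it is.

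### The interim toxicity rule (stop at 5 or more of 13) does not have the stated 80% power at α = 5%: it stops with probability 64.7% at a 40% toxicity rate and 9.9% at a 20% rate

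*Protocol article*

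**What the plan says.** All of this is in the protocol article, section on safety and discontinuation of treatment.

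- **Reference rate.** The rate of severe acute gastrointestinal toxicity under standard treatment "was estimated to be 20" per cent. The increase to be detected is to 40%.
- **Stated performance.** The check takes place "after having recruited about one third of the total number of patients", and the increase "should be detected with a power of 80% at a level of significance of α = 5% in one interim analysis".
- **Source design.** An optimal two-stage design, cited to a reference, "suggested to do an interim analysis after n1 = 15 patients among a total of 43". Its boundary at that look was more than 5 affected patients.
- **Adjustment.** "Since the calculated sample size was n = 37, these numbers were adjusted to n1 = 13 and r1 = 4".
- **Rule in use.** "the study should stop for toxicity after 13 patients if ≥ 5 patients would have developed a severe acute gastrointestinal toxicity".

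The article gives no toxicity boundary for a second stage, at 43 or at 37 patients, and no error rates for the adjusted rule.

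**The concern.** The text attaches a power and a significance level to a single look, and then changes the look. The 80% and 5% were set as targets for a design with 43 patients. The boundary in use comes from shrinking that design's first stage to fit 37. Binomial error rates do not scale with sample size, so the adjusted rule needs its own figures, and none are given.

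This is the only numerical toxicity stopping rule in the article. The trial tests a dose-escalated combination and makes avoiding a marked increase in toxicity part of its aim. A reader who relies on the sentence will believe that passing the look at 13 patients leaves a one-in-five chance of having missed a doubling of severe toxicity, and that a needless stop has a 5% chance. If both are wrong, continuing past 13 patients reassures less than claimed, and a stop at 13 is weaker evidence of excess toxicity than claimed.

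**Working it through.** **Inputs**, all from the section on safety and discontinuation of treatment: acceptable rate 20%; rate to detect 40%; stated power 80% and α 5%; source rule more than 5 of 15 within 43; rule in use 5 or more of 13 within 37.

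**Check of the method.** The section on sample size estimation uses an exact one-sided binomial test for efficacy: 24 or more controlled of 37, with 50% against 70%. The same calculation gives α = 4.9% and power = 80.7%, so that part of the plan reproduces. I then applied the method to the toxicity rule.

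**Step 1: the scaling.** 15 × 37/43 = 12.9, taken as 13. 5 × 37/43 = 4.3, taken as 4. The adjusted pair is thus what proportional rounding gives.

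**Step 2: the rule in use.** With X the number of patients with severe toxicity among 13 and p the true rate,

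P(stop) = 1 − Σ C(13, k) p^k (1 − p)^(13 − k), summed over k = 0 to 4.

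- p = 0.20: 1 − (0.0550 + 0.1787 + 0.2680 + 0.2457 + 0.1536) = 1 − 0.9009 = **0.099**, against the stated 0.05.
- p = 0.40: 1 − (0.0013 + 0.0113 + 0.0453 + 0.1107 + 0.1845) = 1 − 0.3530 = **0.647**, against the stated 0.80.

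The stated figures do not reproduce. The chance of missing a 40% rate at this look is 1 − 0.647 = 35.3%.

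**Step 3: could another cutoff at 13 explain the figures?**

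| Stop if at least | P(stop) at 20% | P(stop) at 40% |
|---|---|---|
| 4 of 13 | 25.3% | 83.1% |
| 5 of 13 (in use) | 9.9% | 64.7% |
| 6 of 13 | 3.0% | 42.6% |

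None gives both. A single exact look first reaches 80% power with α at or below 5% at 35 patients, so a look at one third of 37 cannot.

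**Step 4: could an unshown final look restore them?** Suppose the interim rule is followed by a toxicity boundary at 37. The overall probability of declaring excess toxicity is the interim stopping probability plus whatever the final look adds, so at a 20% rate it is at least 9.9%. For illustration only, a final boundary of 12 gives 12.6% at 20% and 89.8% at 40%; a final boundary of 13 gives 10.9% and 84.6%. Power can pass 80%, but α cannot come down to 5%.

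**Step 5: the reverse orientation.** A two-stage design may instead set out to reject a 40% rate in favour of 20% (non-toxicity 60% against 80%). α is then the chance of accepting the treatment at 40%, and power the chance of accepting it at 20%.

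- 15 of 43, stop at 6 or more, declared too toxic at 12 or more of 43: α = 1 − 0.968 = 3.2%; power = 1 − 0.162 = 83.8%. The source design can meet both targets.
- 13 of 37, stop at 5 or more, too toxic at 10 or more of 37: α = 3.1%, power = 77.1%. At 11 or more: α = 6.0%, power = 83.8%. No final cutoff meets both.

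The scaled rule therefore misses the stated pair in either orientation.

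**The case against.** The strongest defence is that power and α in a two-stage design belong to both stages together. On that view 80% and 5% were only the target from which 15 of 43 was derived, and it is unfair to hold one look to them. Part of this stands. The 35% miss rate applies to the look at 13 patients and not necessarily to the whole trial, since a final look could lift overall detection above 80%. But the article itself assigns the figures to one interim analysis, and steps 4 and 5 show that no final look at 37 recovers both.

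A reader might go further and infer two things that the article does not support:

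- **That the second stage was dropped.** The article shows no second-stage boundary, but it condenses a fuller protocol that is not at hand. Absence here is not evidence of removal.
- **That the source rule fails as well.** As a single look, more than 5 of 15 gives 6.1% at a 20% rate and 59.7% at 40%. As a whole design in the non-toxicity orientation, however, it is compatible with 5%/80% (step 5).

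It can also be said that the secondary endpoints, toxicity among them, are exploratory, and that the rule is clear and workable as written: r1 = 4 and stopping at 5 agree. That is true. The defect lies in the performance claimed for the rule, not in whether it can be carried out.

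**Conclusion.** The point holds for the adjusted rule. As written, 80% power at α = 5% in one interim analysis is wrong for stopping at 5 or more of 13: the exact values are 64.7% and 9.9%. A doubling of severe toxicity is missed at this look about 35% of the time instead of 20%, and the false-stop risk is about double. The calculation assumes only independent patients with a common toxicity rate, all 13 evaluable at the look, and a one-sided reading, which follows from the stated aim of detecting an increase.

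A secondary matter rests on an assumption. If the cited optimal design is Simon's, with minimum expected sample size and no restriction on when the look falls, an exhaustive search at α = 5% and power 80% gives r1/n1 = 3/13 and r/n = 12/43 for 20% against 40%, and 7/11 and 30/43 for 60% against 80%. The total of 43 agrees, but n1 = 15 with r1 = 5 is not the optimum. The reference is not at hand, and another criterion or a restriction on timing could explain the difference, so this is something for the sponsor to check and not an established error.

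**What to change.** Replace the 80%/5% statement with the exact properties of the rule in use, for example: stopping at 5 or more of 13 has probability 9.9% if the true rate of severe acute gastrointestinal toxicity is 20%, and 64.7% if it is 40%. Add that 80% power and α = 5% were targets of the unadjusted two-stage design for 43 patients and were not carried over to 13 of 37.

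If the sponsor wants to keep 80%/5%, the stated figures and the stopping rule must be reconciled by an exact recalculation that counts every planned toxicity look, including the interim stop. The choice of boundary stays with the sponsor and its safety reviewers; none is proposed here, and the cutoffs shown above are only checks. The sponsor should also confirm n1 = 15 and r1 = 5 against the cited source.

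The cost of the restatement is one amended paragraph and no extra patients. The stated power becomes less favourable, and those overseeing safety should be told so.

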[16]. Given the necessity of a slightly lowered intraoperative dose and the aim of a further improvement in local control, it seems reasonable to investigate an increased EBRT dose component in the combined treatment approach. Compared to the postoperative approach, preoperative radiation therapy and the use of improved irradiation techniques seem favourable for the following reasons : Preoperative radiation therapy allows for a more precise target volume definition and delineation with smaller safety margins, reduces toxicity to adjacent organs at risk because of their displacement through the tumor itself, may lead to a devitalisation of tumor cells including a down-sizing effect, and may avoid a treatment delay due to postoperative complications. Considering improved irradiation techniques, intensity-modulated radiation therapy (IMRT) has been shown to result in improved target coverage and reduced dose to adjacent organs at risk compared to conventional irradiation, as shown in several diseases including retroperitoneal sarcoma
[17,18], especially if complex shaped target volumes have to be treated
[19]. Further on, IMRT offers the opportunity to reduce overall treatment time using an integrated boost concept with simultaneously increased dose per fraction in parts of the target volume which are at increased risk for incomplete resection during planned surgery.

Therefore, the primary aim of this trial is to investigate the value of dose-escalated preoperative IMRT followed by surgery with an intraoperative electron boost to reduce the local recurrence rate without a markedly increased toxicity. This combination yields total doses which should be able to control even microscopic residual disease without harm to the adjacent organs at risk.

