### Patient selection and inclusion/exclusion criteria

A minimum of 37 patients fulfilling the inclusion criteria listed below should be enrolled in this trial. Only patients meeting all of the inclusion criteria and missing all of the exclusion criteria (see Table
1) are considered for admission to the trial. Accrual will be stopped after the calculated sample size of the per-protocol population is reached (see statistical considerations).

**Table 1 T1:** Inclusion and exclusion criteria

**Inclusion criteria**	**Exclusion criteria**
written informed consent	missing written informed consent
histologically confirmed, primary or locally recurrent soft tissue sarcoma of the retroperitoneal space	missing histological conformation of soft tissue sarcoma
judged as at least marginally resectable	Desmoid Tumors (aggressive fibromatosis), Gastrointestinal Stroma Tumors (GIST)
absence of distant metastases	judged as gross incomplete or not resectable
tumor size ≥ 5 cm	incomplete staging
	presence of distant metastases
	prior radiation therapy to the abdominal region
	participation in another clinical interventional study
	inflammatory bowel disease

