### Treatment assignment and schedule

All patients eligible for the trial after pre-treatment evaluation (see inclusion/exclusion criteria, Table
1) who gave written informed consent are registered in the trial and assigned to the same treatment regimen (see Figure
1). They receive immobilization and treatment planning examinations for neoadjuvant intensity-modulated radiation therapy (IMRT) either at the Department of Radiation Oncology at the German Cancer Research Center or the University of Heidelberg. Neoadjuvant intensity-modulated irradiation starts within 6 weeks after registration and is carried out in 5 fractions per week for 5–6 weeks using an image guided, stereotactic, intensity-modulated approach up to a total dose of 50–56 Gy. Reevaluation including restaging and assessment of toxicity takes place within 2 to 4 weeks after the last fraction. Surgical resection of the tumor including Intraoperative Radiation Therapy (IORT) with a single dose of 10–12 Gy is carried out within 6 weeks after the end of neoadjuvant irradiation at the Department Surgery in cooperation with the Department of Radiation Oncology at the University of Heidelberg. After postoperative recovery, all patients will be assigned to regular follow up visits either at the Department of Radiation Oncology at the German Cancer Research Center or at the Departments of Surgery or Radiation Oncology.

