### Assessment of toxicity

Acute radiation toxicity will be assessed according to Common Terminology Criteria for Adverse Events Version 3.0 (CTCAE 3.0) during the time period from the first day of neoadjuvant radiation treatment until 3 months after surgery. Late radiation toxicity will be scored according to CTCAE 3.0 and RTOG criteria. Toxicity will regularly be evaluated by clinical and laboratory examinations at least once a week during neoadjuvant external beam radiation therapy and the first follow up visits at discharge of the Department of General Surgery and after 3 months. Late toxicity will regularly be scored during every further regular follow up visit.

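### The toxicity stopping rule (≥5 of 13) has 65% power and a 9.9% false-stop rate, not the stated 80% and 5%

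*Protocol article*

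**What the plan says.** All of this is in the Protocol article; no SAP is available.

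- **Target.** Safety and discontinuation of treatment takes 20% as the rate of severe (grade ≥3) acute gastrointestinal toxicity under standard treatment. It says that an increase to 40% "should be detected with a power of 80% at a level of significance of α = 5% in one interim analysis".
- **Design as calculated.** A cited optimal two-stage design led the authors to "do an interim analysis after n1 = 15 patients among a total of 43 and to stop for toxicity when more than r1 = 5".
- **Rescaling.** "Since the calculated sample size was n = 37, these numbers were adjusted to n1 = 13 and r1 = 4".
- **Rule as fixed.** "Therefore, the study should stop for toxicity after 13 patients if ≥ 5 patients would have developed a severe acute gastrointestinal toxicity".

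The section gives no recalculated error rates for the rescaled rule. The Background makes toxicity part of the primary aim: "to reduce the local recurrence rate without a markedly increased toxicity".

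**The concern.** The section names two error rates and then fixes a rule on 13 patients. Thirteen patients are too few to separate 20% from 40% at 5% and 80%, and the numbers were scaled down from another design with no sign that the error rates were checked again.

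This is the only formal toxicity rule the article states, in a dose-escalation trial that aims to avoid a marked rise in toxicity. A reader who trusts the stated figures will think that passing the look is stronger evidence of safety than it is, and that a needless stop is rarer than it is.

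The issue is the stated properties of the rule. It is not that toxicity goes unseen: under Assessment of toxicity, patients are assessed at least weekly during irradiation, at discharge and at 3 months.

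**Working it through.** **Inputs** (Protocol article, Safety and discontinuation of treatment): acceptable rate 20%; unacceptable rate 40%; stated power 80% and α 5%; first design ≥6 of 15, total 43; rescaled rule ≥5 of 13, total 37.

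**1. The rescaling.** 15 × 37/43 = 12.9, rounded to 13. 5 × 37/43 = 4.3, rounded to 4. So the rescaled numbers agree with simple proportion, which does not preserve error rates.

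**2. Error rates of the look.** With X ~ Binomial(13, p), P(stop) = P(X ≥ 5) = 1 − P(X ≤ 4).

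- p = 0.20: 1 − (0.0550 + 0.1787 + 0.2680 + 0.2457 + 0.1535) = 1 − 0.9009 = **0.099**
- p = 0.40: 1 − (0.0013 + 0.0113 + 0.0453 + 0.1107 + 0.1845) = 1 − 0.3531 = **0.647**

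The stated figures are 0.05 and 0.80, so they are not reproduced.

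**3. Neighbouring cut-offs.**

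| Look | Stop at 20% | Stop at 40% |
|---|---|---|
| ≥4 of 13 | 0.253 | 0.831 |
| ≥5 of 13 (the rule) | 0.099 | 0.647 |
| ≥6 of 13 | 0.030 | 0.426 |
| ≥5 of 15 | 0.164 | 0.783 |
| ≥6 of 15 (before rescaling) | 0.061 | 0.597 |
| ≥7 of 15 | 0.018 | 0.390 |

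No cut-off at 13 or 15 meets both targets. The smallest single look that does is ≥12 of 35 (0.034 and 0.805), which is almost the whole trial.

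**4. What a pass shows.** The look reaches 80% power only at a true rate of 46%. A pass with 4 of 13 has an exact one-sided 95% upper limit of 0.57, so it does not exclude 40%.

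**5. Could an unseen second stage rescue the figures?** For any later bound, P(stop at either stage) ≥ P(stop at the first). At a true 20% the whole rule therefore stops with probability at least 0.099 (at least 0.061 for ≥6 of 15). Final bounds at 37 after ≥5 of 13:

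| Final bound | Stop at 20% | Stop at 40% |
|---|---|---|
| ≥11 of 37 | 0.162 | 0.940 |
| ≥13 of 37 | 0.109 | 0.846 |
| ≥14 of 37 | 0.102 | 0.791 |
| ≥17 of 37 | 0.099 | 0.675 |

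Power can be restored; the 5% cannot.

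**The case against.** The strongest reply is that 80% and 5% belong to a complete two-stage design, and that its second bound may stand in the full protocol. That is fair for power: the 0.647 describes the first look alone, and a final bound such as ≥13 of 37 would lift it to 0.846. The absence of that bound from a condensed article is no error. But it does not help the 5%, which is already exceeded at the first look.

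A second reply is that the authors may have set the design up on the rate of patients without toxicity (60% against 80%). Then 5% is the risk of accepting a 40% regimen, and 80% is the chance of accepting a 20% one. False stops would have a budget of 20%, which 0.099 does not exceed. The original 15 of 43 fits this: ≥6, then ≥12, accepts a 40% regimen with probability 0.032 and stops a 20% regimen with 0.162. So does ≥5 of 13 followed by ≥10 of 35 (0.0499 and 0.192) or ≥11 of 38 (0.0485 and 0.176). Totals above 37 are possible, since the article says "A minimum of 37 patients fulfilling the inclusion criteria listed below should be enrolled in this trial".

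This explanation is plausible, and under it the fault would lie more in the wording than in the rule. Two things count against it. The text attaches 80% to detecting the rise to 40%, which is the opposite assignment. And the total the section rescales to is 37, where the swapped reading also misses, if narrowly: ≥11 accepts a 40% regimen with probability 0.060 (limit 0.05), and ≥10 stops a 20% regimen with 0.229 (limit 0.20).

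**Conclusion.** The concern holds. As the section is worded, the stated 80% and 5% are not the properties of the rule it fixes. For ≥5 of 13 they are 64.7% and 9.9%: a 40% regimen passes with probability 0.353 instead of 0.20, and a 20% regimen is stopped about one time in ten instead of one in twenty.

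The power shortfall applies to the single look and could be made good by a second stage that is not shown. The excess over 5% cannot, given the section's own meaning of α as a false detection at 20%. With the two errors swapped, a final bound at 37 still fails, though other totals would succeed. The calculation assumes only independent patients with a common toxicity rate.

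**What to change.** **1. Correct the sentence.** Keep ≥5 of 13. Replace the stated power and significance level with the look's actual probabilities, 0.099 at 20% and 0.647 at 40%, and say which error each figure is. This changes nothing in conduct.

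**2. Deal with the second stage.** If the full protocol has a second-stage bound, print it with the joint stopping probabilities. If it has none and 80% detection is wanted, add one later cumulative bound on the same event. An example is to pause accrual for review at ≥9 of the first 26. Together with ≥5 of 13 this stops with probability 0.124 at 20%, 0.472 at 30% and 0.825 at 40%. After a pass at 13, a 40% regimen is caught at 26 with probability 0.504. Both looks lie below 37, so these figures hold if enrolment goes beyond it.

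Step 2 is optional and has a price. It needs a short amendment and one more count of toxicity already recorded, with no extra patients or visits. It raises the false-stop probability further, from 0.099 to 0.124. A later bound costs less there: ≥10 of 28 gives 0.114 and 0.811.

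It also spares few patients. Acute toxicity is scored "during the time period from the first day of neoadjuvant radiation treatment until 3 months after surgery", and surgery "is carried out within 6 weeks after the end of neoadjuvant irradiation". With 5–6 weeks of irradiation, up to 6 weeks to surgery and 3 months after it, the window is about 5–6 months. The accrual rate is not given. Assuming 0.5 to 1 patient a month, about 3 to 6 further patients are enrolled before a bound is known to be reached. Expected enrolment at a true 40%, with a cap of 37:

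| Further patients enrolled | ≥5 of 13 only | Plus ≥9 of 26 |
|---|---|---|
| 0 | 21.5 | 19.5 |
| 3 | 23.4 | 22.0 |
| 6 | 25.4 | 24.5 |
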